### Weight and Obesity

An important predictor of health is being overweight or obese. A 2014 review [16] cited the ALSWH papers on weight. Among the
findings, it was found that the proportion of obese individuals rises until the
approximate age of 65 years and then falls [16].
Overweight women are significantly more likely to develop hypertension, heart disease,
asthma, diabetes, depressive symptoms, and polycystic ovary syndrome, and to report
hysterectomy [16]. Women who gained at least 5 kg
over three years reported more menopausal symptoms [16]. The review further reports that individuals well over 60 years of age who
are overweight have an increased chance of developing foot problems, arthritis,
incontinence, declining physical functioning, acute health events, and stroke [16]. The exception to this pattern of disease
susceptibility is osteoporosis, “because the increased load on the skeleton of high body
mass index (BMI) individuals promotes higher bone mineral density” [17].

A potentially worrying point from the perspective of future population health was that in
the 1973-1978 cohort, the 18-year-olds gained approximately 200 grams/year more weight
than did the 23-year-olds [16]. In that 1973-1978
cohort, having a partner added 1.8 kg, and delivering a first baby added 4.0 kg over 10
years [16]. Lower levels of education, working
full time, and having a mother with lower education were also associated with gaining
weight [16].

The 1973-78 cohort will be approximately 8 kg heavier in middle age than the 1946-1951
cohort was. Consistent with the pattern documented by Gomersall et al [16], the Australian Bureau of Statistics reports that
obesity in the population at large peaks at a 35% prevalence at age 65 and then drops to
25% at age 80 [18]. The absence of being
overweight or obese is a predictor of good health, but currently the prevalence of being
overweight or obese is increasing on a worldwide basis [13].

### Health and Behavior Change

There is a plethora of associations between adhering to health guidelines and better
health outcomes, as described in a major ALSWH report [19]. The report shows that women appear to be able to reduce their intake of
clearly harmful substances (eg, smoking, alcohol; whether the latter is beneficial in
moderate doses or not) and their adherence to screenings is consistently high and stable,
or rising [19]. However, in practice it seems
currently impossible to improve people’s daily behaviors of eating less or exercising more
on a population-wide level. In fact, the opposite seems to be the case with Australians:
the percentage of overweight and obese adults is continuously increasing [18], which is a process that seems to be happening in
other countries as well [13]. Interventions that
empower women to address factors of diet, weight management, stress, and mood will likely
be most effective in improving their health.

Good health practices are well known to medical science; the issue is less one of knowing
*what* to do than knowing *how* to increase interest and
action in adopting a healthy lifestyle overall among the wider population. For example,
even diagnosis of a chronic disease (eg, heart disease, diabetes, asthma, breast cancer,
arthritis, or depression) does not lead to improved levels of physical activity [20]. Such a diagnosis in itself is not generally
adequate to induce women to improve their health behavior; although some women do make
improvements, this gain is offset by those whose behavior actually worsens [20]. Counselling from doctors has been shown to work
for high-risk patients [21], but is not being
implemented on a level that would improve population health. In addition, adherence to
doctors’ guidelines for chronic ailments is typically 50% or less [22]. A substantial group of women who are managing to adopt good
health practices would therefore be of great interest to medical science and those
responsible for public health, especially if the women’s lifestyle skills and habits are
teachable and transferable. Our goal is to study participants in a program called
Universal Medicine (UM), to determine whether they have health advantages over women at
large.

### Universal Medicine

UM was founded in 1999 by [name], with the stated goal of, “providing
Complementary Health & Healing Services that are Universal in their approach towards
medicine and healing” [23]. Although [name] has
no background in medicine or healing, as of 2015, approximately 200 men and 500 women were
coming regularly to workshops and seeking treatments from UM-accredited practitioners.
[name] describes UM’s mission as follows:

Through practical philosophies that inspire more self-caring and self-loving choices in
daily life, Universal Medicine supports people to explore their overall well-being, the
development of energetic awareness, and the depth they can bring to their quality of
life and relationships [23]

UM teachings are delivered in the form of lectures, audio recordings, and treatments from
UM clinics. Regular courses, workshops, and retreats are conducted throughout Australia
and internationally. Individual participation levels range widely from consuming one or
more webcasts per year to regular physical attendance at events in North Eastern New South
Wales, Australia or in Frome, Somerset, United Kingdom, which receives approximately 700
regular visitors, including a number of health care professionals.

Over time the authors of this paper became aware of the fact that the large majority of
participants in UM appear to lose weight with little or no effort and yet also report
gains in vitality, as evidenced by observations that participants seem to be able to work
or study for longer periods of time. These changes occur despite the fact that neither
weight loss nor increased vitality is ever explicitly considered or targeted during UM
events. Informal surveys have also indicated that very few members of the group eat gluten
or dairy, drink alcohol or smoke, or consume caffeine. These individuals appear to have
less added sugar and salt in their diets than the normal population does, and also seem to
have little or no difficulty maintaining such a diet.

If these observations are accurate, and if the skills and behaviors associated with UM
participants’ dietary choices and weight loss are transferable to the population at large,
then UM holds a key to very substantial decreases in population health expenditure via
reductions in obesity levels and decreased consumption of alcohol and tobacco. UM also
differs from the norm in its attitude toward women’s health. The numerous and varied
menstrual health issues that women encounter are not treated as nuisances to be managed or
as illnesses to be cured, but as messages from the body that a change in attitude or
lifestyle, or both, is needed. Such changes may be substantial at times, and do not
supplant (but rather augment) visits to registered medical practitioners and adherence to
prescribed treatments.

If this group of women is particularly skilled at managing menstrual health issues, and
if these skills are transferable, then because menstrual symptoms like dysmenorrhea have
prevalence rates as high as 90% [24] and
menstrual symptoms are widespread [25,26], there would be further substantial population
health benefits.

[name] describes the lifestyle associated with UM as *The Way of the
Livingness*, and *Livingness* is described as follows:

In a nutshell The Livingness is simply about living as our true selves... It is our
ability to live and express who we truly are inside, and taking this into our day to day
life. Everything we do say or think and every action we take or do not take contributes
to our Livingness. Our choices, actions and inactions have a direct effect on our
health, physical body, planet and each other. They can be the cause of our greatest
healing or harm [27]

### What is Taught by Universal Medicine?

The core teaching of UM is that our bodies are a source of truth. An introductory course
(Livingness 1) teaches how to *connect* to one’s body and to experience the
consequences of that connection. The next course (Livingness 2) addresses emotions we have
absorbed in the past. For example, a commonly used term is *feeling sick to our
stomach* from emotions, and the extension of that everyday wisdom in UM is that
some of the effects of emotions may linger much longer than the physical symptoms. The
third course (Livingness 3) shows how to deal “with the sabotaging hindrances that prevent
the real you from being in the fore” [28],
showing that the quality in which everyday actions are performed can make a substantial
difference to one’s well-being. Each of these courses can be completed in one day. In
addition, UM presents training in its healing modalities [29], which consists of approximately 10 philosophical lectures in
Australia annually, and three 5-day retreats annually.

### Possible Universal Medicine Effects

A medical doctor who treats a number of UM participants reported to one of the
researchers (CS) that the participants are particularly able to take on a treatment plan
and adhere to it. In addition, UM-affiliated women also appear more prone to adhere to
health guidelines that are very similar to government-recommended ones. A visual gallery
of the typical changes UM participants experience is available [30].

Hence, there is a possibility that the group is above average or even well above average
in a substantial number of physical and mental health indicators. UM has developed a
number of modalities that are complementary to medicine (ie, not developed within a
mainstream medical environment). Evaluating these intervention techniques is beyond the
scope of this survey; however, a randomized controlled cross-over trial of one of the UM
modalities, chakra-puncture, is underway. A randomized controlled trial of another UM
modality (esoteric connective tissue therapy) has received ethical approval from the
University of Queensland, with a published protocol paper [31].

### Female Menstrual Symptoms

A further substantial, but under-investigated, area of women’s health is common menstrual
symptoms. Approximately 80% of women in an ALSWH study [32] reported experiencing premenstrual syndrome, and 60% reported dysmenorrhea
over the 12-year period in which members of the cohort were aged 22-27 years at the start
and 34-39 years at the end. However, some women experienced increasing prevalence, others
had decreasing prevalence, and some had constant high or low prevalence [32]. These findings suggest that there may be
external or internal factors influencing these symptoms, and invites the possibility of
changing these factors. For example, smoking increases menstrual symptoms and
miscarriages, with odds ratios increasing with numbers of cigarettes smoked and younger
age of smoking onset [33].

Women who have fewer menstrual symptoms or conditions have a reduced rate of
hysterectomies [34]; hence, reducing these
symptoms and conditions may have positive implications for the cost of health care. There
is evidence that some female health issues are associated with choices women make in their
lives. Herber-Gast et al [35] showed that both
night sweats and hot flushes are positively associated with education, weight, smoking,
drinking, premenstrual tension, diabetes status, and early age at first pregnancy. These
associations were present whether or not the women were peri-menopausal or menopausal.

Women who are 45-50 years old experience physical declines, with those who are
peri-menopausal or on hormone replacement therapy reporting substantially stronger
declines (expressed in reduced SF-36 scores [36])
compared with those who remained premenopausal [37]. Therefore, a group of women whose physical health does not decline when
their menstrual status changes, even after accounting for age, may be of interest, as
might a group with a consistent drop in these symptoms.

### Objectives

The proposed survey will investigate whether women who participate in UM have a superior
health profile compared with the respondents to the ALSWH. These data would allow a
conclusion as to whether UM is worth investigating further to assess the presence of any
causal links between specific aspects of the program and improved health.

## Methods

### Design

A quantitative cross-sectional survey design will be used to collect data via an online
survey. No directly identifying data (name, address, or birthdate) will be collected;
however, indirectly identifying data such as partial medical history and age in years will
be collected. Hence, parts of the data will not be available for inclusion in the public
repository. Age will be presented as a range, and medical history data will be
excluded.

A recruitment flow diagram is presented in Figure 1. Recruitment will be undertaken by sending emails to a general information
mailing list of approximately 650 members, of whom approximately 72% are female, who are
targeted as regular UM events visitors. A second list of women who participated in UM-run
women’s workshops (approximately 350 members with substantial overlap to the first email
list) will also be used. In addition, visitors to several UM events will be given flyers
with the same introductions given in the email circulars. These three methods are expected
to reach over 90% of the target population. The same recruitment strategies used in
previous surveys led to 482 and 393 respondents, representing 89% and 94% completion
rates. The availability of the survey is to be approximately 7 weeks.

**Figure 1 figure1:**
[figure not shown]
Recruitment flow diagram.

### Preliminary Focus Groups

As a starting point in developing the survey for the proposed study, two of the
researchers (CS and VM) created three focus groups: (1) women in menses, (2)
peri-menopausal women, and (3) menopausal women. Each group met four or five times via
audio conferencing. The 15 participants were aged 18-72 years and were from Australia, the
United Kingdom, Germany, and New Zealand. The education level of these women ranged from
school-leaver to PhD and included a registered nurse, midwife and physiotherapist, an
unregistered health practitioner, an exercise physiologist, and a university lecturer. Two
members had a PhD. All 15 participants tested later versions of the survey.

Two menstrual attitude questionnaires [38,39] were investigated for possible use, but the tone
of these questionnaires implies that menstrual health issues are problems to be minimized
or avoided. This perspective did not agree with the experience of the women in the focus
groups, who considered menstrual health issues useful, and thought that supportive signals
from the body should be heeded; therefore, at the women’s suggestion, we decided to create
a new questionnaire.

Focus group members read through the two existing menstrual attitude questionnaires and
worked with the researchers to develop further questions based on recommendations from the
researchers. Questions that achieved consensus were taken into the first draft and offered
to the other focus groups as suggested questions for their part of the survey. This
process was then repeated through 4 or 5 meetings, until the questions became stable.
There was substantial overlap in questions among the three groups because, according to
the focus groups, even women in their earlier menopausal years still have reproductive
health issues. The developed questionnaire included objective items regarding physical and
mental health symptoms and actions taken, and the participants’ attitudes toward their
female health issues.

All three focus groups worked cooperatively to offer their opinions on which of the ALSWH
questions to adopt to keep the survey to an acceptable length, while including as many
ALSWH questions as possible. The focus was on questions that the researchers felt would
yield the most relevant information about the respondents. One difficult issue was food,
because the ALSWH questions are lengthy and were deemed not very relevant to the
UM-affiliated respondents (eg, few UM respondents eat potatoes). Therefore, a short
question about food items and their frequency of use and a question about current alcohol
consumption were added. The focus group participants stated that they were in various
stages of reducing their caffeine, added sugar, salty food, dairy, and alcohol
consumption. The food question is designed to elicit which stage of reduction each
participant is undertaking, if any. The question was adopted from a smaller biostatistics
student project survey that had been developed with respondent feedback, so the food
question was clearly understood by focus group members.

### Survey Development and Administration

This study emphasizes women’s health, and the survey will only be distributed to female
UM respondents, who constitute over 70% of the UM population. The survey is comprised of
two parts: (1) the newly developed menstrual attitudes questionnaire; and (2) the
selection of questions commonly used in the ALSWH [40], to enable comparisons of the UM respondents to the ALSWH population.

The survey will be completed online using the *survs.com* survey platform
[41]. Issues of a personal or sensitive nature
are regularly and openly discussed at UM events, although anyone who opts out of any
discussion is fully supported. To maintain this spirit of support, the survey was designed
so that a respondent can skip any question that she does not wish to answer. The consent
form at the beginning of the survey also makes it clear that the survey can be terminated
at any time.

The ALSWH was chosen for comparison purposes with Australian women, as the estimated mean
age of UM participants is the late 40s, and one of the ALSWH cohorts had their first
particularly voluminous survey done in 1996, when the cohort’s ages ranged from 45-50
years. The second survey (in the 1998 ALSWH cohort) then filled in a number of gaps so
that it was possible to extract the bulk of the comparative questions from those two
surveys.

#### The Respondent Population

The respondent population is approximately 500-600 women who, as users of complementary
medical services, may have had a similar profile to women who use alternative
practitioners (ie, more likely to be middle-aged, have poorer health, and a higher usage
of conventional medicine) [42]. On the basis of
some researchers’ observations and informal surveys, the population’s average age is now
in the high 40s, they have lost substantial weight since joining UM activities, and may
have higher than average levels of vitality.

#### Final Composition of the Study Survey

After consultation with the focus groups, it was decided that all participants would
answer the same selection of questions from the ALSWH, plus the newly developed question
about food. Early versions of the survey were completed by individual members of the
focus groups, and their feedback was incorporated into the survey. When the survey was
nearing its final version, 10 of the focus group members completed it, and their
feedback was also taken into account.

The first section of the survey asks for consent and confirms that the respondent is at
least 18 years of age. Respondents are also asked about the date of their first UM event
and their overall level of participation in UM. This section comprises 4 items. A major
part of the survey for the proposed study is the SF-36 [36] questionnaire, which is also part of the ALSWH. The SF-36 is
used to assess parameters of physical and mental health. In the proposed study, all
items of the SF-36 will be used. Further ALSWH-employed scales used in the survey are
questions from the Center for Epidemiologic Studies Depression Scale [43,44],
Perceived Control Scale [45], Kessler
Psychological Distress Scale [46], and the
Multi-Item Summed Score for Perceived Stress [47].

On the menstrual attitudes section of the survey, menopausal women answer 42 questions,
peri-menopausal women answer 54 questions, and women in menses answer 48 questions.
Those who have never had any periods are invited to answer the menopausal women’s
questions. Women self-select into the group that they think best fits their situation;
however, if after choosing a group, they find that the questions do not appear to apply
to them, they can back out of the survey and choose a different group.

The first set of questions consists of a list of symptoms with a response scale
including *Yes*, *definitely/Yes*,
*sometimes/No*, *not much/No*, and *not at
all*, which is the same as that in the widely used Women’s Health
Questionnaire [48]. This response scale was
adopted after several more complicated response schemes were tried and discarded to
reduce satisficing [49]. The survey contains
24, 26, and 26 menopausal, peri-menopausal, and menses symptom questions, respectively
(of which 13 are common to all three groups). The survey also contains 24, 29, and 16
menstrual attitude questions, respectively (of which one is common to all three groups
and seven are common to menopausal and peri-menopausal groups). The attitude questions
use a 5-point Likert-type response scale ranging from “strongly disagree” to “strongly
agree”. Multimedia Appendix 1 presents the
derivations of the questionnaire items. A copy of the survey is provided in Multimedia Appendix 2.

The members of the focus group who tested the survey took approximately 75 minutes to
complete it, but did not feel that this was excessive. The survey is similar in length
to the ALSWH full surveys that are held once every 3 years. To make this study’s survey
questions more comparable with those on the ALSWH, wherever possible the former have
retained precisely the same wording as the latter, so the responses can be evaluated
using the tools adopted by ALSWH-associated researchers [50].

At the time of publication of this protocol, data collection has been completed.

## Results

### Menstrual Attitudes Questionnaire

The validity and reliability of the developed questionnaire will be assessed using
Cohen’s kappa [51-53]. Factor analyses for the questions common to all respondents will
be used to ascertain the underlying factors for symptom questions. If the number of
respondents is sufficient, the same will be attempted for the attitude questions and
symptoms questions that are not common to all three menstrual statuses [54,55].
These preliminary validation steps may support the development of a draft menstrual
attitudes questionnaire that can then undergo a full process of validation.

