**Objective:**

This survey investigates whether the approximately 500 women associated with UM exhibit
health status significantly above the norm. As part of this investigation, questions for
a newly developed menstrual attitudes questionnaire will also be evaluated.

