**Results:**

The validity of the menstrual attitudes questionnaire will be evaluated with Cohen’s
kappa. ALSWH respondents and UM participants will be compared, using unweighted
regression or regression weighted or normalized by age, education, and interest in
alternative treatments (to increase comparability), as appropriate. Analyses will
determine whether UM-related variables (being a UM participant, length of UM
participation, number of UM events attended) are associated with: differences in the
number of major health events and health symptoms experienced; SF-36 physical and mental
health scores; body mass index; and consumption of alcohol, tobacco, sugar, salt,
caffeine, and dairy.

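### Cohen's kappa is the only statistic named for the new questionnaire's validity and reliability, but the single survey described gives it no pair of ratings to compare

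*Protocol article*

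**What the plan says.** The abstract's Objective gives the questionnaire a secondary role: "questions for a newly developed menstrual attitudes questionnaire will also be evaluated". Two places fix the method. Under Menstrual Attitudes Questionnaire the article says "The validity and reliability of the developed questionnaire will be assessed using Cohen’s kappa". The abstract's Results repeats it for validity alone: "The validity of the menstrual attitudes questionnaire will be evaluated with Cohen’s kappa".

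The Design section describes the data source: "A quantitative cross-sectional survey design will be used to collect data via an online survey". On identification it says "No directly identifying data (name, address, or birthdate) will be collected", and adds that indirect identifiers (partial medical history and age in years) are collected. On timing it says "The availability of the survey is to be approximately 7 weeks". Final Composition of the Study Survey states that data collection is complete. It also says that the attitude items "use a 5-point Likert-type response scale ranging from" strong disagreement to strong agreement, while the symptom items have four ordered responses.

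The Menstrual Attitudes Questionnaire section also plans factor analysis: for the symptom questions common to all respondents and, if numbers allow, for the attitude questions and the symptom questions that are not common. It calls these steps preliminary to a full validation.

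**The concern.** Kappa is a coefficient of agreement. It needs each woman to be classified twice on the same categories: by two raters, on two occasions, by two equivalent items, or by an item and a criterion. The article names kappa for both properties and never says which two classifications it would compare, and the design it describes supplies one. This is more than a detail that an article leaves to a fuller document, because the statistic has been chosen and the design shown does not feed it.

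At stake is the evidence for a new instrument. Menstruation-related attitudes and symptoms are listed among the variables to be related to SF-36 scores and BMI (Comparative and Detailed Analyses). The Discussion makes the link between attitudes and health status the survey's second step. If the named step cannot be run, either no reliability evidence appears or a substitute is chosen after the data are in hand.

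**Working it through.** The article gives no sample size, power or target value for the questionnaire evaluation, so there is no figure to reproduce. The check is structural.

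**Step 1: what kappa needs.** kappa = (po − pe)/(1 − pe), where po is the observed agreement between two classifications of the same subjects and pe is the agreement expected by chance from the marginal frequencies. One rating per woman gives one set of marginals and leaves po undefined.

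**Step 2: possible sources of a second classification.**

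| Source | What the article describes |
|---|---|
| Retest | None. One survey, open about 7 weeks (Design). Repeat surveys appear only as a possible later longitudinal study (Issues with the SF-36 Instrument). |
| Linkage between occasions | No direct identifiers; some indirect ones; no linkage code (Design). |
| Second rater | None; the survey is self-completed. |
| Duplicate or equivalent items | None named. |
| Criterion for attitudes | None. Two existing menstrual attitude questionnaires were examined and set aside (Preliminary Focus Groups). |
| Focus-group testing | Members tried successive versions and gave feedback, which was taken into account (Final Composition of the Study Survey). No paired ratings are described. |

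No row supplies a described pair.

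**Step 3: how little one administration says about kappa.** Assume, for illustration only, uniform marginals that would be the same on both occasions.

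- 5-category attitude item: pe = 5 × (0.2 × 0.2) = 0.20. With po = 0, kappa = (0 − 0.20)/(1 − 0.20) = −0.25. With po = 1, kappa = (1 − 0.20)/(1 − 0.20) = 1.00.
- 4-category symptom item: pe = 4 × (0.25 × 0.25) = 0.25. With po = 0, kappa = (0 − 0.25)/(1 − 0.25) = −0.33. With po = 1, kappa = 1.00.

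A single administration leaves the whole range from −0.25 (or −0.33) to 1.00 open. The expected 200-400 respondents per item estimate the marginals better but do not narrow that range.

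**Step 4: what the factor analysis covers.** It needs no second rating. The firm commitment is to the symptom items common to all three menstrual groups, of which there are 13. The attitude items are conditional on numbers. The groups have 24, 29 and 16 attitude items (menopausal, peri-menopausal, in menses) and one is common to all three, so 23, 28 and 15 respectively are not. Factor analysis describes structure; it does not by itself give the reliability estimate that the article assigns to kappa.

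**The case against.** The strongest reply is that the aim is modest and the article is a condensation. The questions are only to be evaluated as an additional aim, the steps are called preliminary, and a full validation is to follow. Factor analysis is planned alongside kappa. The main question, health status of UM participants against the ALSWH, does not use kappa. All of this stands, and it lowers the severity.

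It also rules out several stronger readings that a reader might infer:

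- *That no usable pair exists.* The survey and the item derivations are in Multimedia Appendices 1 and 2, which are not shown. The same women answer new symptom items and ALSWH symptom items, so some pairs may ask the same thing on the same categories. A retest subsample in a fuller protocol cannot be excluded either. The supportable statement is that no pair is described.
- *That the questionnaire objective cannot be met.* Factor analysis can meet part of a preliminary evaluation. Only the kappa-based validity and reliability assessment fails as written.
- *That the survey is fully anonymous, so linkage is impossible.* Indirect identifiers are collected. The article simply describes no linkage.
- *That kappa can never bear on validity.* Agreement between an item and a criterion classification is a legitimate use. Here no criterion is described.
- *That kappa would be unweighted and so ignore the response order.* The article does not say which form is meant.
- *That the ten focus-group members who completed a near-final version would act as a small retest.* Nothing proposes this, so no precision calculation on them describes a planned analysis.

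None of these points supplies the missing pair of ratings. Kappa remains the only statistic named for reliability, and nothing described lets it act.

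**Conclusion.** The stated method does not fit the described design. Kappa is assigned both validity and reliability, yet the article shows one completed self-report administration and names no second classification. As written, kappa cannot support either claim, at any sample size. The planned factor analysis can speak to structure, firmly for the common symptom items and conditionally for the attitude items, but it leaves reliability without an estimate.

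This should be fixed before results for the questionnaire are reported. It does not undermine the comparison with the ALSWH, and the regressions are not made conditional on kappa. The conclusion assumes that the article's description of measurement occasions is complete. It would soften if the appendices or a fuller protocol named item pairs or a retest subsample. The kappa ranges in the working rest on assumed uniform marginals and only illustrate the gap.

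**What to change.** In the Menstrual Attitudes Questionnaire section, and correspondingly in the abstract:

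1. Replace kappa as the main statistic with an internal-consistency coefficient suited to ordinal items, with a 95% CI, reported by menstrual-status group. The choice of coefficient can be left to the authors.
2. Keep the planned factor analysis as the evidence on structure.
3. For construct validity, use correlations with the standard scales already collected (SF-36, depression, perceived control, psychological distress, perceived stress), with the expected directions stated beforehand.
4. Keep kappa, weighted for the ordered responses, only for within-survey item pairs that are named and ask the same thing on the same categories.
5. State that test-retest reliability and criterion validity are not assessed and are left to the later full validation.

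The cost is wording and routine analysis, with no new data. The downside is that the validity and reliability claim shrinks to internal consistency, structure and construct correlations. As collection is already complete, the choices should be fixed and dated before the items are analysed, or reported as made afterwards.
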